### Recruitment

2.4

#### Quantitative research section

2.4.1

One month prior to the formal survey, recruitment will be promoted through posters within the hospital and other means, and medical staff from relevant departments will contact potential research participants via telephone, face-to-face interviews, or online communication.One day prior to the formal survey, research participants will be contacted to briefly explain the research content and confirm the baseline enrolment time.On the day of baseline enrollment, explain the purpose, methods, and follow-up arrangements of the study to the participants, commit to anonymizing the questionnaire data to protect privacy, and obtain informed consent. Explain that the service account usage fees will be covered by the project, and that participants will receive a gift each time they participate in the survey.

#### Qualitative research section

2.4.2

In the quantitative research, two categories of patients were selected based on their baseline PHQ-9 scores: those with higher scores and those with lower scores. The selection process ensured representativeness across key demographic characteristics such as gender and age, resulting in an initial list of interview participants.Prior to the formal interviews, patients were contacted through multiple ways to explain the content of the qualitative research and obtain informed consent, and interview times were scheduled.On the day of the interview, the research objectives, methods, and recording permissions and privacy protection measures were reiterated to the participants. After obtaining consent, the interview was initiated, and a participation gift was provided at the end.

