Currently, Swanson’s Theory of Caring is widely applied in studies involving women who have experienced abortion. Jansson et al. (26) conducted semi-structured interviews with women who experienced early abortion or missed abortion between 18 and 20 weeks of pregnancy. The researcher analyzed the data using the five processes of Swanson’s Theory of Caring. The results indicated that care beneficial to women includes empathy, emotional support, maintaining dignity, competence, and meeting individualized needs. Adolfsson et al. (27) applied Swanson’s Theory of Caring to the rehabilitation of women who experienced early miscarriage. The results indicated that midwives who followed up with women after miscarriage using this theory as a guide were able to reduce sadness scores. Palas et al. (28) found that personalized care based on Swanson’s Theory of Caring could alleviate patients’ physical, emotional, behavioral, and cognitive sadness symptoms, as well as reduce future negative emotions, depression, and anxiety.

The study aims to evaluate the effectiveness of an Artificial Intelligence-Empowered Mobile Health intervention using Swanson’s Theory of Caring on negative psychological states such as depression and anxiety in women after abortion through a mixed-methods study, while also examining clinical examination and test indicators and semi-structured interview data from patients.

The specific objectives are:

To evaluate whether the two-week AI mobile health intervention program reduces psychological distress in women after miscarriage.To evaluate the acceptability of an AI-based mobile health intervention in primary care for women after abortion.

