### Design

2.1

The study will use a mixed-methods study design and will be conducted at the Inner Mongolia Maternity and Child Health Care Hospital from 2025 to 2026. A randomized controlled trial with two parallel groups will compare the effectiveness of an Artificial Intelligence-Empowered Mobile Health intervention guided by Swanson’s Theory of Caring on psychological distress (such as depression, anxiety, and stress) in women after abortion. The intervention will last for two weeks, with participants undergoing questionnaires, physical examinations, and individual interviews at baseline and at two weeks to explore changes in psychological distress. The study flowchart is shown in **Figure 1**.

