### Sample size

2.3

This study is a mixed-methods research. The intervention group will receive Artificial Intelligence-Empowered Mobile Health interventions, while the control group will receive standard care. Based on previous research findings, nursing interventions based on Swanson’s Theory of Caring have been shown to significantly reduce depression and anxiety levels in women who have experienced abortion, and can serve as a reference for effect size (29). The Minimum Clinically Important Difference (MCID) was selected as a reduction of ≥5 points on the Patient Health Questionnaire-9 (PHQ-9), which is considered clinically meaningful (30). The standard deviation (SD) is based on previous studies showing that the SD of PHQ-9 in the abortion population is approximately 6–8 points. The test level α = 0.05 and test efficacy 1-β = 0.90 are set, and according to the randomized controlled trial mean comparison formula:

$$n=\frac{{\left(Z_{\alpha /2}+Z_{\beta }\right)}^{2}\cdot 2\sigma^{2}}{\Delta^{2}}$$

The sample sizes for each experimental group are equal. Z_α/2_ = 1.96, Z_β_ = 1.28, σ = 8, Δ = 5 in this example. The sample size for each group can be calculated as n = 42 people. Considering the follow-up missing rate, the sample size for each group is increased to 50 people, for a total of 100 people.

Qualitative research is guided by the principle of information saturation, meaning that interviews with patients are stopped once a certain number of participants have been reached and no new information is emerging. Therefore, this study does not specify a minimum sample size for qualitative research.

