**Specific Methods:**

Conduct inquisition, physical examinations, and necessary auxiliary examinations, and promptly provide feedback and explanations of the results to patients.Collect patient responses and impressions regarding the use of Artificial Intelligence-Empowered Mobile Health through semi-structured interviews, and guide completion of follow-up questionnaires.

**Swanson’s Theory of Caring:** Doing for, Enabling.

**Intervention providers:** Researcher.

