What specific functionalities of Artificial Intelligence-Empowered Mobile Health did you use?Which Artificial Intelligence-Empowered Mobile Health functionalities had a positive effect on your health, and which ones had no effect or even had a negative effect?How did using Artificial Intelligence-Empowered Mobile Health affect your mental health? What do you think caused these effects?With the help of Artificial Intelligence-Empowered Mobile Health, what did you learn about post-abortion care?To what extent did you trust the health information provided by Artificial Intelligence-Empowered Mobile Health? Did you find its responses reliable? Why?’How did you feel when Artificial Intelligence-Empowered Mobile Health attempted to comfort or encourage you? Do you perceive this emotional support as genuine? Please elaborate on your feelings.”What were your expectations of Artificial Intelligence-Empowered Mobile Health prior to using it? How did its actual performance differ from your expectations?’Compared to support provided by healthcare professionals or family/friends, what unique aspects did you find in interacting with Artificial Intelligence-Empowered Mobile Health? Which form of support do you prefer? Why?’

Patient demographic information will be collected through the case system and self-designed questionnaires. (**Table 1**).

**Table 1 T1:** Variables and measures collected at every time point.

Variables	Date source	Measures	Baseline(T0)	Post-intervention(T1)
Intervention preparation	/	Eligibility screen, Informed consent and Allocation	✓	
Covariates	Baseline questionnaire	Sociodemographic information	✓	
	Baseline questionnaire and Follow-up questionnaire	Behavioral information	✓	✓
Primary outcome	Baseline questionnaire and Follow-up questionnaire	Patient Health Questionnaire-9 (PHQ-9)	✓	✓
Secondary outcome	Baseline questionnaire and Follow-up questionnaire	Generalized Anxiety Disorder-3, GAD-3	✓	✓
		Perceived Stress Scale 4, PSS-4	✓	✓
		Perceived Social Support Scale Short Form, PSSS-SF	✓	✓
		Body Image-Acceptance and Action Questionnaire-5, BI-AAQ-5	✓	✓
		Posttraumatic Stress Disorder Checklist for DSM-5, PCL-5	✓	✓
		EuroQol Visual Analogue Scale, EQ-VAS	✓	✓
	Clinical examination and laboratory tests	Ultrasound, human chorionic gonadotrophin, HCG		✓
Qualitative results	semi-structured interviews	Effect of the trial		✓

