### Ensuring intervention compliance

2.8

To encourage subject compliance, we will (1) fully explain the subject’s responsibilities during the observation period at the time of recruitment and signing of the informed consent form. At the same time, we will strive to build strong relationships with participants with the aim of promoting mutual trust. (2) Throughout the study, researchers will provide short- and long-term self-care guidance and comprehensive health education after abortion. (3) The research team will assess the interaction between the intervention group and the system on a weekly basis. This is to ensure that participants are fully engaged. Regular monitoring can identify any issues or dropouts promptly, enabling the team to take corrective actions and maintain participant engagement.

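### The acceptability objective rests on interviews whose selection rule ignores use of the AI and is not limited to the intervention arm, so women who used it little or stopped may be few or absent

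*Protocol article*

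**What the plan says.** The Background section gives two specific objectives. The second is "To evaluate the acceptability of an AI-based mobile health intervention in primary care for women after abortion".

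The outcomes in section 2.6 and Table 1 include no acceptability scale, usability scale or usage measure. The interviews are the only listed source that asks women about the AI. Section 2.5.4, Phase 3, places them at follow-up: "Collect patient responses and impressions regarding the use of Artificial Intelligence-Empowered Mobile Health through semi-structured interviews". Table 1 lists them under qualitative results as "Effect of the trial", at the post-intervention time point. Section 2.1 describes them differently, as "individual interviews at baseline and at two weeks to explore changes in psychological distress".

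The selection rule is in section 2.4.2: "two categories of patients were selected based on their baseline PHQ-9 scores: those with higher scores and those with lower scores". It adds that "The selection process ensured representativeness across key demographic characteristics such as gender and age". The number of interviews is left to saturation, and section 2.3 states that "this study does not specify a minimum sample size for qualitative research".

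Use of the service is already tracked. Under Phase 2 in section 2.5.4, interaction records are reviewed every day. Section 2.8 adds: "The research team will assess the interaction between the intervention group and the system on a weekly basis".

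**The concern.** Non-use and early abandonment are central evidence on whether a digital service is acceptable. A baseline depression score is taken before the service is used and does not show who took it up. The interviews can therefore reach saturation among women who used the service without hearing from those who did not, and the text has no provision for noticing this.

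The interview frame is also loose. Section 2.4.2 draws interviewees from the quantitative study as a whole, while the questions printed in section 2.6.2 are about the AI, which the control group does not receive.

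Finally, the objective names primary care, but sections 2.2 and 2.2.1 enrol outpatients having surgical abortion at one maternity hospital. No result from this sample can speak to primary care.

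At stake is the second objective. The PHQ-9 comparison between arms is not affected.

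**Working it through.** The plan gives no figure on this point, so there is none to reproduce. The check has two parts.

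**1. The sections side by side**

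| Question | Where | What the text gives |
|---|---|---|
| What must be answered? | Background, objective 2 | Acceptability of the AI |
| Which listed source asks about it? | 2.5.4 Phase 3; 2.6.2; Table 1 | Interviews at T1 only |
| Who is interviewed? | 2.4.2 | Higher or lower baseline PHQ-9, plus demographics |
| Which arm? | 2.4.2 | Not stated |
| Is use known to the team? | 2.5.4 Phase 2; 2.8 | Yes, reviewed daily and weekly |
| Is use part of selection? | 2.4.2 | No |
| Are women who stopped, or who miss T1, provided for? | 2.4.2; 2.5.4 Phase 3 | No |

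The baseline interviews mentioned in section 2.1 precede use and cannot inform acceptability. Gender, one of the two demographic examples, cannot vary because all participants are women.

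Taken literally, a frame of both arms (50 + 50) would on average give half of the interviews to women who never had the service: 6 of 12.

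**2. Possible size (illustration)**

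The intervention arm of 50 is from section 2.2. The share of low users, their attendance at T1, the number of interviews and the ratings are assumptions. All regular users are assumed to attend.

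With N reachable women, L of them low users, and m interviews drawn without regard to use:

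P(no low user) = C(N − L, m) / C(N, m)

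*Case A: 15 low users (30%), m = 12.*
- All attend: N = 50, L = 15. Expected low users interviewed = 12 × 15/50 = 3.6. P(none) = C(35,12)/C(50,12) = 0.007.
- 8 of the 15 miss T1: N = 42, L = 7, a share of 7/42 = 17%. Expected = 12 × 7/42 = 2.0. P(none) = C(35,12)/C(42,12) = 0.075. (This 42 is 50 − 8 and is unrelated to the 42 per group in section 2.3.)

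*Case B: 10 low users (20%), m from 10 to 20.*

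Assume that 80% of regular users and 30% of low users would call the service acceptable. With low-user share s, expected acceptability among the women reachable at T1 is 0.80 − 0.50 × s. In the whole arm s = 10/50, which gives 70%.

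| Low users attending T1 | N, L | s | P(none), m = 10 to 20 | Expected acceptability among reachable women |
|---|---|---|---|---|
| 10 of 10 | 50, 10 | 20% | 0.083 to 0.003 | 70% |
| 5 of 10 | 45, 5 | 11% | 0.27 to 0.04 | 74% |
| 2 of 10 | 42, 2 | 5% | 0.58 to 0.27 | 78% |
| 0 of 10 | 40, 0 | 0% | 1 | 80% |

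With full attendance there is no expected upward shift, only a chance of missing low users. Any shift comes from low users missing T1.

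**The case against.** The strongest reply is that a list built on a baseline score is neutral to later use, so low users enter it roughly in proportion. Stopping the account is not the same as missing T1. T1 is also the clinical follow-up visit with ultrasound and HCG. Women are contacted beforehand, those in the intervention arm are accompanied, and a gift is given at each survey. The documents give no reason to assume that half of the low users would stay away. This stands, and it rules out a stronger reading that a reader might infer: that acceptability is bound to be overstated. The PHQ-9 split has no fixed direction of its own.

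A reader might also infer that the interaction data serve compliance alone, or that the guide shuts out criticism. Neither is supported. Sections 2.5.3 and 2.5.4 also use the data to detect concerns and severe symptoms and to update the knowledge base. The guide asks about absent or negative effects, trust and unmet expectations, and it is open-ended. A woman who gave up on the service could answer it if she were reached.

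It can further be said that interviews run to saturation are not meant to estimate an unbiased proportion, and that choosing by depression score suits the distress purpose in section 2.1. Both are fair. But the same interviews are the only listed source for objective 2, and for that purpose the rule omits the most relevant characteristic.

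Nor is this just detail that an article leaves to a fuller document. The article states its rule, and the rule does not fit this objective.

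**Conclusion.** The point holds as a modest, cheaply repaired weakness in how objective 2 is answered. On the text alone, without assumptions: the interviews are the only listed source on acceptability, selection takes no account of use, the frame is not limited to the intervention arm, and the primary-care target does not match the sample.

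The size is conditional. Under the assumptions above, the chance of interviewing no low user is 0.007 with full attendance and 0.075 when 8 of 15 low users miss T1 (12 interviews in both cases). With 20% low users and 10 to 20 interviews it ranges from 0.003 with full attendance to 0.58 when only one in five of them attends. The upward shift in apparent acceptability is nil with full attendance, about 4 percentage points when half of those low users attend, and at most 10 when none do. The documents give no usage or attendance rate, so these figures show a range and are not a forecast.

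**What to change.** 1. In section 2.4.2, limit the frame for the AI interviews to the intervention arm.
2. Add logged use over the two weeks (regular, low, stopped) as a sampling criterion alongside baseline PHQ-9.
3. Offer a remote interview to women who stopped using the service or missed T1.
4. In section 2.6 and Table 1, report the interaction data already reviewed as a quantitative acceptability result: the proportion of women active in week 1 and in week 2, and the number of queries.
5. In objective 2, replace the primary-care wording with the setting studied: outpatients having surgical abortion at one maternity hospital.

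The cost is protocol wording, a summary of existing logs, and a few more invitations to women who are harder to reach.

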### Interventions

2.5

#### Control group: standard care

2.5.1

The control group was not completely blank. At the time of enrolment, patients in the control group received standard oral health education, including explanations of the surgical procedure and precautions, routine preoperative examinations, and guidance on postoperative precautions. Any questions or concerns raised by patients were answered in detail.

#### Intervention group: standard care + artificial intelligence-empowered mobile health

2.5.2

Based on the physiological recovery cycle after abortion and the critical time window for screening complications, this study was designed as a two-week continuous intervention. The intervention protocol was developed by a multidisciplinary team comprising public health experts, clinician doctors, nurses, psychologists, and statistical analysts, integrating expertise from all relevant fields. The core intervention method employs Artificial Intelligence-Empowered Mobile Health, guided by Swanson’s Theory of Caring as a theoretical framework. The two-week intervention period is divided into distinct phases, each of which is strictly implemented by the fundamental care dimensions of this theory.

#### Preparation before intervention

2.5.3

To overcome the “hallucination” and “fabrication” problem of LLMs, this study formed a multidisciplinary team of medical professionals to build a structured Knowledge-based Question Answering (KBQA) and put it into use through an FAQ robot. The team comprised specialists from multiple medical disciplines, including two obstetricians and gynecologists, three registered nurses with over five years’ experience in obstetrics and gynecology, a clinical psychologist, and a public health specialist. The research team will randomly sample approximately 5% of AI-patient interaction logs daily for review. Based on the five core processes of Swanson’s theory (Knowing, Being with, Doing for, Enabling, Maintaining belief), the theoretical adherence of interaction content will be assessed. Should any deviation be identified, the team will immediately convene to revise knowledge base content, ensuring the sustained quality and theoretical consistency of the intervention.

The knowledge base covers core content such as medical knowledge about abortion, post-operative diet, and exercise guidance etc.(The daily checklist is detailed in the Supplement1). The knowledge base is deployed on the Coze, where the LLMs can self-learn and provide 24-hour professional Q&A services via a WeChat Official Account. After each query, the system recommends three related questions to guide patients into deeper interaction. Researchers regularly analyze interaction data to identify patients’ concerns and severe physiological and psychological symptoms, contact attending physicians when necessary, and continuously update the knowledge base according to the quality of Q&A and user needs.

After conducting multiple model comparisons and adjustments, the “Doubao-pro-32k” was ultimately selected for use in this study. The “Doubao-pro-32k” model is an advanced large language model (LLM) provided by the Coze platform, specifically the version identified as Doubao-1.5-thinking-pro/250415. It is a text-only model that excels in specialized domains such as mathematics, programming, and scientific reasoning, as well as general tasks like creative writing. The model has demonstrated competitive performance on several authoritative benchmarks, including AIME 2024, Codeforces, and GPQA, achieving results that are comparable to or near the top tier of current industry standards.

This decision was based on research indicating that Doubao-pro-32k achieves a higher overall score and demonstrates outstanding performance in knowledge application among similar LLMs used in medical applications (31). After the initial development is completed, the experts’ department of obstetrics and gynecology will be invited to evaluate the quality of the LLM’s responses to ensure accuracy and professionalism. Additionally, the WeChat Official Accounts only access the user’s WeChat nickname, avatar, signature, and location; the account does not involve any related privacy data.

#### Specific intervention strategies

2.5.4

**Phase 1: From outpatient visit to surgery day.**

**Swanson’s Theory of Caring:** Knowing.

**Intervention providers:** Attending doctor, researcher.

**Intervention content:**

Patients fully understand the intervention process and measures of the study.Doctors and researchers fully understand the patient’s medical history and psychological needs.

**Specific Methods:**

Study Introduction and Trust Building: During outpatient visits, the researcher and attending doctors jointly provide patients who meet the inclusion criteria and are willing to participate in the study with a comprehensive introduction to the study, thereby establishing an initial trust relationship with the patients.Establishment of Patient Information Records: For patients who meet the study criteria and are included in the study, the researcher guides them in completing electronic questionnaires via Questionnaire Star after signing the informed consent form. Basic medical conditions and laboratory results are recorded in the hospital’s medical record system.In-depth Interview Research: Researchers engage in in-depth communication with patients, asking questions such as “What do you think is the biggest problem you are facing right now?” and “What are your strongest feelings about abortion?” to gain a detailed understanding of the patients’ thoughts and needs.

**Swanson’s Theory of Caring:** Doing for, Enabling.

**Intervention providers:** Researcher.

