**Figure 1 f1:**
[figure not shown]
Flow chart of patient recruitment and study implementation.

The study used a simple randomization method. The steps are as follows: first, in Excel, we used the RAND function to generate a number between 0 and 1. The function is invoked by entering “=RAND()” in any cell and pressing Enter. The generated number determines the group assignment for each patient: if the number is from 0 to 0.5 (excluding 0.5), the patient is assigned to the intervention group; if it is from 0.5 to 1 (excluding 0.5), the patient is assigned to the control group. If the number is exactly 0.5, the process is repeated until a valid random number is obtained.

The blinded method used in this study involves several categories of individuals:

Medical staff in the research department (blinded): responsible for patient recruitment, informing patients of admission and follow-up times and locations, and conducting basic biochemical and imaging examinations for admission and follow-up, they are unaware of patient group assignments.Investigators (blind): Their responsibilities are strictly limited to one-on-one data collection with patients; they do not participate in other research activities to ensure data specificity and accuracy. Investigators are unaware of patient group assignments.Data processing personnel (blind): They receive coded data (Group A/Group B) and are unaware of the specific assignment relationship between Groups A/B and the intervention or control groups.Patients (unblinded): The intervention group is guided by the researcher to follow the Artificial Intelligence-Empowered Mobile Health Official Account and instructed on its use. The control group does not receive this service.System administrator (unblinded): Responsible for online management and answering questions for patients in the intervention group; their service is limited to patients in the intervention group, as only this group receives the Artificial Intelligence-Empowered Mobile Health intervention.

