### Study sample

2.2

A total of 100 participants will be enrolled in this study. The participants in this study were female outpatients who undertook surgical abortion at the Inner Mongolia Maternity and Child Health Care Hospital. This study used continuous enrolment, and prior to the study, patient consent was obtained, and patients were randomly assigned to the intervention group and the control group, with 50 patients in each group, for a total of 100 patients. The inclusion and exclusion criteria are as follows:

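### The baseline PHQ-9 is listed as an intervention step guided by an intervention provider, against the blinded-collection rule, and nothing shown places it before allocation

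*Protocol article*

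**What the plan says.** **Where T0 is placed.** Section 2.5.2, which describes the intervention arm, says: "The two-week intervention period is divided into distinct phases, each of which is strictly implemented by the fundamental care dimensions of this theory". The first of these, in section 2.5.4, is headed "Phase 1: From outpatient visit to surgery day". Its first block (Knowing) names the attending doctor and the researcher as intervention providers. Under that block's methods, after an introduction to the study and before an in-depth interview, comes the questionnaire step: "the researcher guides them in completing electronic questionnaires via Questionnaire Star after signing the informed consent form". The control-arm text (2.5.1) mentions no questionnaire.

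**Who collects it.** Section 2.1 lists investigators as blinded and says of them: "Their responsibilities are strictly limited to one-on-one data collection with patients". Section 2.9 has investigators take participants one-on-one through a uniform electronic questionnaire without prompting answers. Phase 3 of section 2.5.4 again places guidance on the follow-up questionnaires among intervention tasks, with the attending doctor and researcher as providers.

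**When allocation happens.** Section 2.2 says: "prior to the study, patient consent was obtained, and patients were randomly assigned to the intervention group and the control group". Table 1 has a row "Eligibility screen, Informed consent and Allocation" ticked in the T0 column, above the PHQ-9 row, which is ticked in the same column.

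**Blinding and outcome.** Section 2.1 lists patients as unblinded. The primary outcome is change in depression level (Abstract), measured by PHQ-9 (2.6.1.1). Section 2.7 plans GEE to compare the groups.

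**The concern.** A baseline can be relied on in a randomised comparison when it cannot depend on the assigned arm. That is guaranteed if it is completed before allocation is known, under the same conditions in both arms. Here the questionnaire appears as a component of one arm's intervention, and the person guiding it helps to deliver that intervention. The respondent is unblinded and reports her own symptoms.

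If the order in practice is allocation first, a woman may answer PHQ-9 knowing that she will or will not get the AI service. If the researcher guides T0 in the intervention arm and a blinded investigator does so in the control arm, the collection conditions also differ by arm. Either route could move T0 in one arm only. Because the primary outcome is a change, that movement enters the treatment estimate directly. More participants would not remove it.

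**Working it through.** **1. The sections side by side**

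| Question | Section 2.5.4 | Sections 2.1 and 2.9 |
|---|---|---|
| Who guides the questionnaire? | The researcher, a named intervention provider | Investigators; by 2.1 blinded and limited to data collection |
| What is the step part of? | Phase 1 of the intervention strategy | Data collection, the same for all participants |

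Both cannot describe the same T0 assessment. The Phase 3 wording on follow-up questionnaires repeats the conflict, so the T0 sentence is not an isolated slip.

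**2. The order of allocation and T0**

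- Section 2.5.4 places T0 after consent and does not mention allocation.
- Section 2.2 names consent and assignment together and does not mention T0.
- Table 1 has allocation and PHQ-9 in one column; row order is not a stated sequence.
- Figure 1 might show the order but is not available here.

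Allocation before T0 is therefore possible on the text shown, and so is the reverse.

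**3. What an arm-related shift would do**

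The plan gives no figure for this, so there is none to reproduce. Suppose reporting at T0 in the intervention arm is shifted by s points and T1 is unaffected.

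- Difference in change (also the group-by-time term of a GEE with two time points): the arm difference at T1 minus that at T0, so the bias has absolute size s.
- Baseline-adjusted estimate: the T1 difference minus ρ times the T0 difference, with equal SDs at T0 and T1 and correlation ρ. The bias has absolute size ρ·s. For s = 1 and an assumed ρ of 0.3 to 0.7, this is 0.3 to 0.7 points.

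Against the planning difference Δ = 5 (section 2.3), a 1-point shift is 1/5 = 20% in the change score.

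**4. Illustration: false-positive rate with no true effect**

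Inputs from section 2.3: two-sided α = 0.05, and 42 and 50 per group as the plan's group sizes. The SD of 8 there is the SD of PHQ-9. Using 8 for the change is an assumption, because SD of change = 8·√(2(1−ρ)), which equals 8 only at ρ = 0.5.

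Standard error = 8·√(2/n): 1.746 for n = 42 and 1.600 for n = 50.

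False-positive rate (normal approximation) = P(Z > 1.96 − s/SE) + P(Z < −1.96 − s/SE).

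| s | n per arm | s/SE | Normal approximation | t-test |
|---|---|---|---|---|
| 1 | 42 | 0.573 | 0.088 | 0.087 |
| 1 | 50 | 0.625 | 0.096 | 0.095 |
| 2 | 42 | 1.146 | 0.209 | 0.205 |
| 2 | 50 | 1.250 | 0.240 | 0.236 |

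Sensitivity to ρ, for s = 1 and n = 50 (normal approximation): at ρ = 0.3 the change SD is 9.47 and the rate 0.083; at ρ = 0.7 the change SD is 6.20 and the rate 0.127.

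**5. Illustration: a shift in the other direction**

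If T0 in the intervention arm is lowered by b while the true T1 difference is 5, the difference in change is 5 − b. With SD 8 and 50 per group, power falls from 0.88 (b = 0) to 0.71 (b = 1) and 0.47 (b = 2). With 42 per group the values are 0.82, 0.63 and 0.41.

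The shifts are assumed. No section gives a value for s, b or ρ.

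**The case against.** The strongest reply is that nothing shows a contaminated baseline. A reader might infer that T0 is taken after allocation and after first contact with the intervention. The document does not support that:

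- The questionnaire sentence says only that it follows consent.
- The preceding trust-building step is offered to "patients who meet the inclusion criteria and are willing to participate in the study with a comprehensive introduction to the study". By that wording it applies to both arms, so it cannot by itself create an arm difference.
- The questionnaire step is worded "For patients who meet the study criteria and are included in the study", again without limiting it to one arm.
- The in-depth interview, account set-up and AI demonstration are all listed after the questionnaire.

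Section 2.9 already describes uniform collection by investigators, and the flow chart or a fuller protocol may fix the order. The error rates rest on assumed shifts, and the t-test on change is not the planned GEE.

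These points stand, and they rule out saying that T0 does follow allocation or that the trial has an inflated type I error. They do not remove the contradiction over who collects T0, which lies in the text itself: section 2.9 supports section 2.1 and so sharpens the conflict with 2.5.4. A flow chart giving the order would not resolve that conflict either. Nor does wording that can be read as common enrolment explain why the step sits in the intervention strategy with intervention providers named.

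**Conclusion.** The point holds in this form: the T0 questionnaires, PHQ-9 among them, are written as a Phase 1 intervention step guided by an intervention provider. This contradicts the sections that give collection to blinded, data-only investigators, and no text shown secures T0 before allocation. With unblinded women and a self-reported change outcome, that leaves a route by which the baseline could depend on the arm.

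The bias would be s points in the difference in change and about ρ·s after baseline adjustment; s and its sign are unknown. The rates of about 9% for a 1-point shift and 20 to 24% for a 2-point shift show sensitivity only. They assume a change SD of 8 and a test on change, and do not estimate this trial's error rate. If T0 is completed before allocation and in the same way in both arms, the bias is zero.

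The protocol should be changed on this point. Confidence is medium, because the order may be given in the figure that could not be seen.

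**What to change.** In sections 2.2 and 2.5.4 and in Table 1, state a single sequence:

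1. Consent.
2. All T0 questionnaires, with the blinded investigator and in the same way in both arms.
3. Generation and disclosure of the allocation.
4. Phase 1 contact.

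In Table 1, give allocation its own step after the T0 questionnaires. Take the T0 questionnaire out of the intervention description, so that 2.5.4 agrees with 2.1 and 2.9 on who collects it, and bring the Phase 3 wording on the follow-up questionnaires into line.

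The cost is small: steps are reordered around the baseline visit, with existing staff and no new data. If some women have already been enrolled, record for each whether T0 preceded disclosure of the arm and who guided it.
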